#### Subjective measures

3.7.5

Momentary subjective stress and relaxation are assessed repeatedly using single-item Likert-type ratings from 0 to 10 at predefined time points, including upon arrival, after stress induction, baseline, each auditory condition, and at the end of the session. Emotional state during the MEG procedure is additionally assessed using the Self-Assessment Manikin (SAM; Bradley and Lang, 1994), a pictorial measure of affective valence, arousal, and dominance. Before the MEG recording, participants complete questionnaires assessing sociodemographic and personal data, positive and negative affect using the German version of the Positive and Negative Affect Schedule (PANAS; Breyer and Bluemke, 2016), perceived stress using the German version of the Perceived Stress Scale (PSS-10; Schneider et al., 2020), relaxation state using the German Relaxation State Questionnaire (RSQ; Steghaus and Poth, 2022), imagery ability using the Plymouth Sensory Imagery Questionnaire (PSIQ; Andrade et al., 2014), and dispositional mindfulness using the German version of the Five Facet Mindfulness Questionnaire (FFMQ-D; Michalak et al., 2016). After the MEG recording, participants again complete measures of mood and relaxation state (PANAS, RSQ), report prior experience with mindfulness and relaxation exercises, and complete the Multidimensional Assessment of Interoceptive Awareness, Version 2 (MAIA-2; Mehling et al., 2018), to assess general interoceptive awareness. These measures are used to characterize the sample and to explore interindividual variability in subjective, autonomic, neural, and brain–body regulation outcomes.

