### Aims

2.1

Primary:

To characterize acute neural and autonomic regulation during brief mindfulness-based and relaxation-based interventions.To differentiate mindfulness and relaxation in terms of their underlying regulatory processes.

Secondary:

To examine brain–body coupling as a dynamic link between neural activity and autonomic rhythms.To examine autonomic coupling, particularly the coordination between cardiac and respiratory dynamics, across mindfulness, relaxation, and control conditions.To explore speech processing and brief speech production as psychotherapy-relevant extensions of the main paradigm.To identify psychological and lifestyle-related correlates of individual responsiveness.

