#### Mindfulness condition (body scan)

3.6.1

The mindfulness condition consists of a guided body scan exercise based on standardized mindfulness material. Participants are guided to systematically direct attention to different body regions and to observe bodily sensations in a present-focused and non-judgmental manner. The exercise encourages participants to notice bodily sensations without attempting to change them and to gently return attention to the body when distracted. This condition is intended to target interoceptive awareness, attentional regulation, and present-centered awareness.

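### MAIA-2 is taken once, after the body scan and the other two conditions, yet serves as a correlate of responsiveness, so the response itself can colour the score.

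*Protocol article*

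**What the plan says.** Section 3.7.5 (Subjective measures) divides the questionnaires into two sets. Before the MEG recording come the sociodemographic items, PANAS, PSS-10, RSQ, the imagery scale (PSIQ) "and dispositional mindfulness using the German version of the Five Facet Mindfulness Questionnaire" (FFMQ-D). The second set comes at the end: "After the MEG recording, participants again complete measures of mood and relaxation state (PANAS, RSQ), report prior experience with mindfulness and relaxation exercises", and they "complete the Multidimensional Assessment of Interoceptive Awareness, Version 2" (MAIA-2). The stated purpose of MAIA-2 is "to assess general interoceptive awareness". No MAIA-2 administration before the session is described.

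The same section gives the use of the whole set: "These measures are used to characterize the sample and to explore interindividual variability in subjective, autonomic, neural, and brain–body regulation outcomes". This serves a secondary aim in section 2.1, "To identify psychological and lifestyle-related correlates of individual responsiveness", the matching secondary research question in section 2.2, and the interindividual-variability level in section 3.8.

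Section 3.6.1 says of the body scan: "This condition is intended to target interoceptive awareness, attentional regulation, and present-centered awareness".

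**The concern.** A score that is meant to describe what a person brings to the session should be fixed before the session can act on it. Here the order is reversed for the one scale whose construct the body scan sets out to engage. Someone who noticed bodily sensations readily during the scan may afterwards rate their general body awareness higher. Someone who found the scan frustrating may rate it lower. Either way the score moves in the direction of the response, and an association appears even if the underlying trait has nothing to do with responsiveness.

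With a single post-session measurement, no later analysis can separate the trait from the session effect. Section 4.4 says the findings will be used to generate hypotheses about who benefits from what. A MAIA-2 association would be a natural candidate for such a hypothesis, and its direction would be unknown.

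**Working it through.** **Order of events, from the text**

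| Step | Source | Relation to the auditory conditions |
|---|---|---|
| Diagnostic appointment at the outpatient clinic | 3.4.2 | before the laboratory session |
| PSS-10, PSIQ, FFMQ-D, first PANAS and RSQ | 3.7.5 | before |
| Body scan, safe place imagery, podcast in random order | 3.2, 3.5 | – |
| Spoken reflection questions after each condition | 3.5, 3.7.6 | during the sequence |
| Second PANAS and RSQ, prior experience, MAIA-2 | 3.7.5 | after |

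PANAS and RSQ are state measures with a value from before and after, so their late administration is appropriate. FFMQ-D and PSIQ, which serve the same correlate analyses, are collected beforehand. MAIA-2 is the trait scale that is not.

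**Mechanism.** Every participant hears all three recordings (section 3.2), so exposure is constant and cannot by itself produce a correlation between persons. The route is the difference between persons in response, which is the very variable that MAIA-2 is to be correlated with.

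**Illustration of size.** The protocol gives no figure to reproduce: section 3.4.2.1 bases N = 30 on feasibility and states no effect size or SD. Inputs from the document are N = 30, at least 15 per diagnosis, and two-tailed alpha 0.05 (section 3.9.3). The carry-over b is an assumption.

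Let the trait T and the response R be independent, each with SD 1, and let the post-session score be M = T + bR. Then:

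- induced correlation: r = b / √(1 + b²)
- chance of p < 0.05, Fisher approximation: 1 − Φ(1.96 − z) + Φ(−1.96 − z), with z = atanh(r) × √(n − 3)

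Example, b = 0.2 and n = 30: r = 0.2 / √1.04 = 0.196; z = 0.1987 × √27 = 1.032; chance = 1 − Φ(0.928) + Φ(−2.992) = 0.178.

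| b (assumed) | r induced | n = 30, Fisher | n = 30, simulated | n = 15, Fisher |
|---|---|---|---|---|
| 0 | 0 | 5% | 5% | 5% |
| 0.1 | 0.10 | 8% | 8% | 6% |
| 0.2 | 0.20 | 18% | 18–19% | 11% |
| 0.3 | 0.29 | 34% | 34–35% | 18% |
| 0.4 | 0.37 | 53% | 54% | 27% |

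The smallest correlation that reaches significance is 0.36 at n = 30 and 0.51 at n = 15. If MAIA-2 is collected before exposure, b = 0 and the rate returns to 5%.

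**The case against.** **The analyses are exploratory and non-causal.** Sections 2.3.2, 3.8 and 4.4 class the psychological correlates as exploratory and rule out direct causal claims, and the aims speak of correlates and associations. This stands as a limit on the consequences. It does not remove the artefact, because the association itself may be a product of the session.

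**The size is wholly assumed.** This stands. At b = 0.1 the rate is about 8%, close to nominal. One value of b should also not be applied to every outcome. Section 1.3 notes that physiological change may go unperceived and that subjective and autonomic markers can diverge. Carry-over into a questionnaire is therefore plausible mainly for subjective ratings, and less so for RMSSD or MEG power.

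**Late placement may be deliberate, to avoid priming.** This stands in part. A body-awareness questionnaire shortly before the recording could prime attention to the body. Because body attention is the content of only one of the three conditions, the effect need not be equal across them and could reach a primary contrast. That argues against same-day administration before the MEG recording. It does not argue against an earlier visit. The article gives no reason for the placement, and section 4.3 does not list it among the limitations.

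**The mindfulness correlate analysis does not rest on MAIA-2 alone.** Correct: FFMQ-D is measured beforehand.

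A reader might infer two stronger things. One is that prior experience, collected at the same late point, is biased to the same degree. The documents do not support that: it is a report of history, and nothing suggests that a 10-minute exercise changes it beyond some recall error or relabelling. The other is that the session's condition effects are compromised. They are not, because MAIA-2 plays no part in the primary hypotheses of section 2.3.1.

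**Conclusion.** The concern holds for MAIA-2. The measurement schedule leaves a path from response to score, the body scan is directed at the same construct, and the data as planned cannot close that path. The direction of the problem follows from the text; its size does not. The illustrative rates of 8% to 54% at N = 30 rest on an assumed linear carry-over of 0.1 to 0.4 SD per SD of response and on no true trait relation. They show how the bias would behave, not how large it is. The effect is limited to exploratory associations of MAIA-2 with responsiveness, chiefly with subjective response. It is a modest point, worth acting on because it is cheap to prevent and cannot be repaired once a participant has been tested.

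**What to change.** Administer MAIA-2 at the diagnostic appointment described in section 3.4.2, before the laboratory session. Keep PANAS and RSQ where they are. Prior experience can move to the same appointment for convenience, but this is secondary.

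The cost is a few more questionnaire minutes at an existing visit and a gap between MAIA-2 and the session, which is acceptable for a scale meant to describe a general characteristic. Moving it to the questionnaires on the day, before the MEG recording, is the less suitable option because of the priming risk.

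For participants already tested, flag MAIA-2 as measured after exposure, do not interpret it as a pre-existing characteristic that explains response, and add the timing to the limitations in section 4.3. If the late placement is kept, state the reason and apply the same restriction to all participants.

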#### Speech-related measures

3.7.6

After each auditory condition, participants provide brief spoken responses to standardized reflection questions. Speech-related analyses will be exploratory and include two components. First, neural speech tracking during auditory stimulation will be examined using temporal response functions (TRFs), which relate acoustic features of the auditory stimuli to MEG activity and provide an index of neural tracking of spoken audio material. TRF-based neural speech tracking is included as a preregistered stimulus-engagement measure. Second, speech-production features extracted from brief post-condition verbal responses, such as speech rate, pause characteristics, pitch/F0, and voice quality measures, may be analyzed depending on recording quality and the structure of the extracted speech data. These speech-production analyses are exploratory and will be interpreted cautiously, particularly because overt speech can introduce movement and muscle artifacts in MEG recordings. Therefore, speech-production analyses require rigorous artifact handling to support valid interpretation (Abbasi et al., 2021).

#### Preprocessing and data quality

3.7.7

MEG preprocessing will follow established procedures for continuous MEG data and will be implemented using Python-based analysis tools, including MNE-Python (Gramfort et al., 2013). Preprocessing will include signal-space-separation-based noise reduction, filtering between 0.1 and 40 Hz, identification and correction of ocular and cardiac artifacts using independent component analysis, resampling to 100 Hz, and segmentation of the continuous data into condition-specific analysis windows. Components related to cardiac and ocular activity will be identified using the simultaneously recorded ECG and EOG signals and inspected as part of quality control.

For spectral analyses, power spectra will be estimated using Welch’s method, a Fourier-based approach that provides a stable estimate of how signal power is distributed across frequencies (Welch, 1967). These will be summarized within the predefined frequency bands relevant to the preregistered hypotheses. These band-limited power estimates will be averaged across sensors for global analyses and, where applicable, summarized within predefined sensor-level or source-level regions of interest. For neural speech-tracking analyses, preprocessed MEG data will be aligned with the auditory stimulus material and prepared for temporal response function analyses.

Physiological preprocessing will be conducted on the temporally aligned ECG and respiration recordings using Python-based signal-processing tools, including NeuroKit2 (Makowski et al., 2021). ECG preprocessing will include signal cleaning, optional signal inversion where required, R-peak detection, artifact correction of detected peaks, and derivation of interbeat intervals. Heart rate will be calculated from the corrected R-peak series, and HRV will be quantified using time-domain measures, with RMSSD used as the primary HRV metric. Respiration preprocessing will include respiratory signal processing, detection of respiration peaks, and calculation of respiration rate. Physiological features will be extracted for each experimental condition and, where appropriate, additionally summarized in 30-s segments to support data-quality inspection.

Data quality will be assessed separately for neural, cardiac, and respiratory outcomes. Quality-control plots of ECG, respiration, detected peaks, and segment-level physiological values will be visually inspected to identify technical failures, unreliable peak detection, or physiologically implausible values. Missing or unusable data will be identified using outcome-specific quality criteria, including technical recording failure, missing or corrupted channels, excessive MEG artifacts, unusable ECG or respiration signals, unreliable physiological feature extraction, and physiologically implausible values. Data exclusions and available sample sizes will be reported separately for each outcome. When condition-level data are incomplete but sufficient valid data remain for a participant, linear mixed-effects models may be used to retain these participants without requiring complete data for all conditions.

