### Randomization and blinding

3.3

The three auditory conditions are presented in randomized, counterbalanced order using a predefined condition-order scheme implemented in the MATLAB experiment script. Separate condition-order matrices are generated before data collection for the ADHD and depression groups using a random number generator. In the script, each auditory condition is assigned a numerical code: body scan = 1, safe place imagery = 2, and podcast = 3. These numbers are condition codes, not order numbers. For example, [1 2 3] means body scan–safe place imagery–podcast, whereas [2 3 1] means safe place imagery–podcast–body scan. In the ADHD matrix, for example, participant 1 could receive [1 2 3], participant 2 [1 3 2], and participant 3 [2 1 3]. At the start of the experiment, the experimenter enters the participant’s diagnostic group and sequential within-group participant number. The MATLAB script then selects the corresponding row from the predefined matrix and presents the audio files in that order. This procedure supports a balanced distribution of condition orders as far as possible within each diagnostic group and ensures that condition assignment is reproducible and documented. The selected order is saved in the participant log file.

No formal blinding is involved. Participants are not informed about the specific study hypotheses and will be debriefed after participation to minimize expectation-related effects.

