#### Missing data and data quality

3.9.2

Procedures for handling missing or unusable data, for example due to artifacts, will be transparently specified and reported for each outcome. Missing or unusable data will be identified using outcome-specific quality criteria, including technical recording failure, missing or corrupted channels, excessive MEG artifacts, unusable ECG or respiration signals, unreliable physiological feature extraction and physiologically implausible values. Analyses will be conducted on available data, with transparent reporting of data exclusion and sample sizes for each outcome. When condition-level data are incomplete but sufficient valid data remain for a participant, linear mixed-effects models may be used to retain these participants without requiring complete data for all conditions.

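### Visual quality control of per-condition physiological data, with no masking stated, lets exclusions depend on condition and could bias within-person contrasts in either direction

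*Protocol article*

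**What the plan says.** Section 2.3.1 places heart rate, RMSSD and respiration rate, with global MEG band power, among the outcomes of the primary hypotheses.

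Section 3.7.7 (Preprocessing and data quality) sets the level at which the physiological measures are derived and checked: "Physiological features will be extracted for each experimental condition and, where appropriate, additionally summarized in 30-s segments to support data-quality inspection". It then says: "Quality-control plots of ECG, respiration, detected peaks, and segment-level physiological values will be visually inspected to identify technical failures". The sentence goes on to unreliable peak detection and implausible values. The grounds for calling data unusable include "unreliable physiological feature extraction, and physiologically implausible values", and also excessive MEG artefact.

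For MEG components the same section says: "Components related to cardiac and ocular activity will be identified using the simultaneously recorded ECG and EOG signals and inspected as part of quality control". ICA stands in the list of steps before "resampling to 100 Hz, and segmentation of the continuous data into condition-specific analysis windows".

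Section 3.3 (Randomization and blinding) says: "No formal blinding is involved". It adds only that participants are not told the specific hypotheses.

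Section 3.9.2 says: "Analyses will be conducted on available data, with transparent reporting of data exclusion and sample sizes for each outcome". Both 3.7.7 and 3.9.2 allow a mixed model to keep a participant who lacks usable data for some conditions.

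**The concern.** The person doing quality control sees physiological values and decides whether they are credible. The values come from condition-specific windows, they feed the primary autonomic outcomes, and nothing hides the condition. A run of slow breathing or a high RMSSD might be accepted as real in one condition and discarded as artefact in another. Because one condition can be dropped while the participant stays in the model, such a decision acts on one side of a within-person contrast. If a value is removed because of its size, the missingness depends on the missing value itself, and a mixed model does not correct for that.

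The planned reporting is by outcome. The article does not commit to reporting by condition, so an imbalance of exclusions between conditions could go unseen. With a target of 30 participants, and a minimum of 15 per diagnostic group, a few such decisions can matter.

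**Working it through.** **Figure to reproduce.** None. The sample size in 3.4.2.1 rests on feasibility, and the article gives no effect size, standard deviation, power or exclusion rate. What follows is an illustration under stated assumptions.

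**Inputs from the article.** n = 30 (clinical target) and n = 15 (minimum per diagnostic group), section 3.4.2.1; two-sided alpha 0.05, section 3.9.3.

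**Assumptions.** One contrast between two conditions; normal paired differences with mean 0 (true null) and SD 1; k differences excluded; 50,000 simulated samples for each n.

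**Test.** With m = n − k differences left, t = mean / (s / √m), compared with the 0.975 quantile of t on m − 1 degrees of freedom.

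**Worst case: the k least favourable differences are dropped.**

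| n | k | bias (SD) | two-sided error |
|---|---|---|---|
| 30 | 0 | 0.00 | 0.051 |
| 30 | 1 | 0.07 | 0.082 |
| 30 | 2 | 0.13 | 0.139 |
| 30 | 3 | 0.19 | 0.223 |
| 15 | 0 | 0.00 | 0.050 |
| 15 | 1 | 0.12 | 0.092 |
| 15 | 2 | 0.23 | 0.175 |
| 15 | 3 | 0.33 | 0.29 |

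**Milder case: each difference in the lowest 20% of the distribution is dropped with probability 0.25 or 0.5.**

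| n | probability | mean number dropped | bias (SD) | error |
|---|---|---|---|---|
| 30 | 0.25 | 1.5 | 0.08 | 0.070 |
| 30 | 0.5 | 3.0 | 0.16 | 0.139 |
| 15 | 0.25 | 0.75 | 0.07 | 0.058 |
| 15 | 0.5 | 1.5 | 0.15 | 0.085 |

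**Exclusion unrelated to condition: k dropped at random, or by absolute size of the difference.** For k = 0 to 3 the bias is about 0 and the error 0.049 to 0.052 at both sample sizes.

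**Scale.** From the noncentral t, a paired t test at alpha 0.05 has 80% power at d = 0.53 for n = 30 and d = 0.78 for n = 15. The worst-case bias at n = 30 with three exclusions is 0.19 / 0.53 = 36% of the detectable effect; with one exclusion it is 0.07 / 0.53 = 13%.

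**MEG.** Component selection and data rejection need separating. If ICA is run on the continuous recording, as the listed order suggests, removing a component changes all three conditions alike and excludes none. Rejection for excessive artefact can remove data from one condition, so the argument carries over to it.

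**The case against.** Several counter-arguments have force.

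- **The blinding sentence stands in the section on condition order.** What follows it concerns participants. Nothing says whether the quality-control rater sees labels. But the sentence is unqualified, and no masking of any kind is described elsewhere, so the point stands as one about the method as written.
- **Numeric limits and file handling are details that an article leaves out.** This is right as to limits: they may be in the preregistration, which is not shown, and their absence is not held against the plan. The point rests on two things the article does state: visual inspection and no blinding.
- **Much of the inspection is technical.** Two of its three named purposes are recording failure and peak detection, and it follows automated peak detection and correction. The 30-s summaries are also not the condition-level outcomes. This narrows the room for judgement but does not close it, since implausible values are the third purpose and the segments are built from the same signals.
- **No direction is stated.** A reader might infer that slow breathing or high RMSSD is the predicted effect, so that exclusions would favour it. Section 1.4 describes relaxation as aimed at physiological downregulation, but 2.3.1 states only differences between conditions and 3.9.3 uses two-sided tests. An unmasked rater could equally discard extreme values in an active condition and hide an effect.
- **The error rates are not this plan's.** Raters judge levels, not ranked paired differences. Section 3.9.3 plans an omnibus test and then corrected pairwise tests, not one uncorrected t test. This stands; the figures show only how sensitive a sample of this size is.

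**Conclusion.** The concern holds for the ECG and respiration outcomes and for rejection of MEG data for excessive artefact. The method as written lets exclusions depend on condition, and neither reporting by outcome nor a mixed model removes that. Bias is possible, not demonstrated, and its direction is open.

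Its size depends on how many exclusions there are and how selective they are, and the article says nothing on either. Under the assumptions shown, one to three fully selective exclusions at n = 30 give an error of about 8% to 22% and a bias of 0.07 to 0.19 SD. The milder pattern gives 7% to 14%.

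A reader might also infer that the inspection of ICA components is open to the same bias. The article does not support that: components are identified from the recorded ECG and EOG, and ICA is listed before the data are cut by condition.

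This is a correction worth making before quality control starts, because decisions taken with labels visible cannot later be made masked. It does not undermine the design, and the article limits its own inference to mechanistic description (4.4).

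**What to change.** 1. Carry out quality control of ECG, respiration and MEG segments on files given random codes, with condition and order hidden. Conditions already have numeric codes and the order is saved in a log file (3.3), so the link can be held apart.
2. Apply the same criteria to all conditions.
3. Lock the exclusion list before condition labels are merged.
4. Report exclusions by condition as well as by outcome.
5. Add a sensitivity analysis without the plausibility exclusions.

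Steps 4 and 5 are needed even with masking. If a condition truly changes breathing or heart rate, a masked rater using one common limit may still remove more data from that condition.

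The cost is a recoding step in the existing Python pipeline and a little extra analysis and reporting. Nothing changes for participants. That the cost is small is a judgement; the article does not address it.
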